### Voluntary Step Execution Test

To assess the proactive balance function, participants will stand on a single force platform and will be instructed to voluntary step as quickly as possible following a somatosensory cue, given randomly on one of their feet as described in detail in previous articles (Melzer and Oddsson, 2004; Melzer et al., 2007b; Batcir et al., 2018). A total of six trials will be conducted in single-task (ST) conditions, as well as in dual-task (DT) conditions, while performing the Stroop test. The temporal events will be extracted from the step execution data: (a) reaction time; (b) foot contact time; and (c) preparation time (Melzer and Oddsson, 2004; Melzer et al., 2007b). The ICC values for intratester reliability, for older adults, are good to excellent in these step parameters across ST and DT task conditions (0.62–0.88; Melzer and Oddsson, 2004; Melzer et al., 2007c). A quick execution of a step is an early line of defense to avoid falling, which may be considered the most important postural reaction to prevent a fall (Maki et al., 1994; McIlroy and Maki, 1999; Melzer and Oddsson, 2004; Melzer et al., 2007b). We previously found that the step execution test is sensitive to the effects of age in both ST and DT conditions, (Melzer and Oddsson, 2004) identified older adults who reported retrospectively a fall under the dual-task condition but not in single-task condition, (Melzer et al., 2007b) and predicted future falls with no added value to dual- over single-task condition (Melzer et al., 2010b); however, we found that the dual-task paradigm of the voluntary step execution test was able to detect the probability of being seriously injured from a fall (Melzer et al., 2009). In a recent meta-analysis of 54 studies (*n* = 8, 385), Okubo et al. (2020) showed that stepping performance was significantly worse in fallers compared to nonfallers (Cohen’s *d* 0.55, 95% CI 0.48–0.66, *p* < 0.001, *I*^2^ 68%). This was the case for both volitional and reactive step tests. Twenty-two studies (*n* = 3, 503) were included in a diagnostic meta-analysis that showed that step tests have moderate sensitivity (0.70, 95% CI 0.61–0.77), specificity (0.69, 95% CI 0.61–0.77), and area under the receiver operating characteristics (AUROC; 0.76, 95% CI 0.67–0.83) in discriminating fallers from nonfallers.

#### Postural Stability Test and Stabilogram Diffusion Analysis

The participants will be instructed to stand barefoot as still as possible on a force platform in a standardized stance, with their feet close together. There were four 30-s quiet-standing trials with eyes open (EO) and four trials with eyes close (EC) and blindfolded. The center of pressure (CoP) and ground reaction force data will be collected with the Kistler 9287 force platform. Evaluation of balance control will be made using the traditional measure of postural sway in both EO and EC conditions (e.g., ML sway, AP sway, mean sway velocity, and mean sway area). We will also calculate the stabilogram diffusion analysis (SDA) parameters from CoP data [e.g., critical displacement (Cd) and critical time (Ct)]. The transition point between the short-term and long-term behaviors has been termed the Ct, and sway displacement has been termed the Cd at which closed-loop control begins to dominate sway behavior. It was described in detail by Collins and De Luca (Collins and De Luca, 1993; Collins et al., 1995). The ICCs for the CoP sway parameters are excellent in the EC condition: ML sway (ICC = 0.933), AP sway (ICC = 0.946), sway area (ICC = 0.710), sway length (ICC = 0.945; Bauer et al., 2008) The ICC showed fair to good reliability in the SDA parameters: Ds (ICC = 0.79), Dl (ICC = 0.50), Cd (ICC = 0.66), and Ct (ICC = 0.63; Chiari et al., 2000). The postural stability and SDA method have been adopted by several research groups who have shown that the parameters of postural stability and SDA are sensitive to the effects of age (Melzer et al., 2001) old adults who retrospectively reported falls (Melzer et al., 2004, 2010a) and older adults who reported injury as a result of a fall (Kurz et al., 2013).

Also, clinical measurements and questionnaires will be conducted:

(1)The Berg Balance Scale (Berg et al., 1989) assesses balance and fall risk with an excellent interrater (ICC = 0.98) and intrarater (ICC = 0.99) reliability.(2)Late-Life Function and Disability Instrument (Melzer et al., 2007a) is a self-reported function that measures difficulty in performing basic and advanced daily physical tasks with ICCs of 0.91–0.98 for the function component.(3)Short Falls Efficacy Scale-International (Yardley et al., 2005) evaluates fear of falling while performing indoor and outdoor daily activities with an excellent ICC of 0.83.(4)MMSE’s (Folstein et al., 1975) test–retest reliability was excellent (Pearson *r* = 0.98, *p* < 0.001), and its validity was found to be high and significant as well (*r* = 0.77, *p* < 0.0001; *r* = 0.66, *p* < 0.001, for the verbal and performance subscores, respectively).

#### Power and Sample Size Calculation

Since it is well established that perturbation training is effective in improving balance and reducing falls (Sherrington et al., 2019), the primary purpose of this study is to determine the effect of block PBBT on major components of reactive balance control among older adults: fall threshold and multiple-step threshold. Our primary hypothesis is that improvements in reactive balance control following block PBBT will be not inferior to the improvements following random PBBT. We will use the non-inferiority approach. Non-inferiority trials examine whether a new experimental treatment (i.e., block PBBT) is not unacceptably less efficacious than another treatment (i.e., random PBBT) already in use. Our primary outcome measures are the multiple-step threshold and fall threshold that are rarely used as outcome measures although multiple-step threshold levels are shown previously to be independent predictors of a future fall (Hilliard et al., 2008; Eichelberger et al., 2016) and the fall threshold is a novel measure of balance recovery function that seems to be ecologically valid. Both the fall threshold and multiple-step threshold were used as primary outcome measures in our recent study (Handelzalts et al., 2019) where we found that 11 of 11 stroke patients (100%) who participated in the random PBBT intervention improved their fall threshold (from 4.5 ± 2.0 to 6.5 ± 1.3) compared with only four out of 13 stroke patients who participated in the nonperturbation training intervention and that the multiple-step threshold to forward and backward perturbations was improved (from 1.9 ± 1.4 to 3.8 ± 1.7 and from 2.6 ± 1.4 to 4.5 ± 2.1, respectively). The sample size for a non-inferiority trial with a fall threshold and multiple-step threshold was calculated using the formula below (Statistical Solutions Ltd., 2020; nQuery 8—Power Sample Size for Group Sequential Trials version 8.6.1.0).

Sample sizes for each of the primary outcomes are outlined in Table 4. In regard to the fall threshold and the multiple-step threshold (backward), the sample size that was calculated for each group is similar, *n* = 19. A two-group one-sided 0.05 significance level *t*-test will have 80% power to reject the null hypothesis that the block PBBT and random PBBT are not noninferior [the difference in means of the fall threshold and multiple-step threshold (backward), μR − μB, is 2.00 and 1.90, respectively, or farther from zero in the same direction), in favor of the alternative hypothesis that the means of the two groups, i.e., block PBBT and random PBBT, are noninferior, assuming that the expected difference in means is 0.00 and the common standard deviation for the fall threshold is 2.40 and the common standard deviation is 2.00 for the multiple-step threshold (backward; based on an earlier study; Handelzalts et al., 2019). In regard to the multiple-step threshold (forward), the calculated sample size in each group is 8, and a two-group one-sided 0.05 significance level *t*-test will have 80% power to reject the null hypothesis that the block PBBT and random PBBT are not noninferior (the difference in means, μR − μB, is 1.90 or farther from zero in the same direction), in favor of the alternative hypothesis that the means of the two groups are noninferior, assuming that the expected difference in means is 0.00 and the common standard deviation is 1.40 (Table 2). To account for attrition rates reported to be about 25% involving training in older adults, (McMurdo et al., 2000) it was decided to include 25 participants in each group (19 × 1.25 = ~25) for a total of 50 participants.

**Table 4 T4:** Sample size estimation.

	Fall threshold	Multiple-step threshold (forward)	Multiple-step threshold (backward)
Test significance level α (one-sided)	0.05	0.05	0.05
Non-inferiority limit difference, Δ0	2.00	1.9	1.90
Expected difference, Δ1	0.00	0	0.00
Δ0 − Δ1	2.00	1.90	1.90
Common standard deviation, σ	2.40	1.4	2.0
Effect size, δ = |Δ0 − Δ1|/σ	0.833	1.357	0.826
Power, %	80	80	80
Sample size, per group, *n*	19	8	19

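### The non-inferiority limits equal the full gain seen with random PBBT, so meeting the rule shows only that block PBBT did not lose all of it

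*Protocol article*

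**What the plan says.** Under Power and Sample Size Calculation, the protocol defines the purpose of a non-inferiority comparison as showing that the experimental schedule "is not unacceptably less efficacious than another treatment (i.e., random PBBT) already in use". Block PBBT is the experimental arm.

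The same section summarises an earlier study in stroke patients. The 11 patients "who participated in the random PBBT intervention improved their fall threshold (from 4.5 ± 2.0 to 6.5 ± 1.3"). Their multiple-step thresholds to forward and backward perturbations rose "from 1.9 ± 1.4 to 3.8 ± 1.7 and from 2.6 ± 1.4 to 4.5 ± 2.1, respectively". Four of 13 patients without perturbation training improved their fall threshold; their mean change is not reported.

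The null hypothesis for the fall threshold and the backward multiple-step threshold is that the difference in means, random minus block, "is 2.00 and 1.90, respectively, or farther from zero in the same direction". For the forward threshold the difference "is 1.90 or farther from zero in the same direction". Table 4 repeats the limits as 2.00, 1.9 (forward) and 1.90 (backward). The earlier study is cited as the basis of the planning figures. No clinical or statistical argument is given for the size of the limits.

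Under Statistical Analysis, non-inferiority is supported when the lower 95% confidence limits for block minus random, on the post-intervention values of the three primary outcomes, lie above the negative limits. Both intention-to-treat and per-protocol analyses are to be used.

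**The concern.** A non-inferiority limit states how much benefit may be given up before the new treatment counts as unacceptably worse. Here each limit has the same numerical value as the whole before-to-after improvement that the protocol reports for the comparator. On those figures, the largest loss the rule excludes is a total loss.

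At stake is the meaning of the primary conclusion. The rule could be met, and the word non-inferior used, when the data exclude no more than block PBBT achieving nothing. The protocol's own definition promises more than that.

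**Working it through.** **Inputs.** The before and after means, limits, SDs and group sizes come from Power and Sample Size Calculation and Table 4; the decision rule comes from Statistical Analysis. Evaluable numbers are taken as 19 per arm (calculated) to 25 per arm (recruited).

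**1. The plan's own figure.** For a one-sided 0.05 t-test with true difference 0, limit 2.00 and SD 2.40, the noncentral t gives 80.9% power at 19 per arm. The governing sample size of 19 reproduces. The forward figure of 8 also reproduces (limit 1.9, SD 1.4).

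**2. Gain against limit.**

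| Outcome | Gain with random PBBT | Limit | Limit / gain |
|---|---|---|---|
| Fall threshold | 6.5 − 4.5 = 2.0 | 2.00 | 100% |
| Multiple-step, forward | 3.8 − 1.9 = 1.9 | 1.9 | 100% |
| Multiple-step, backward | 4.5 − 2.6 = 1.9 | 1.90 | 100% |

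The fraction of the gain preserved at the limit is 1 − 1 = 0% each time. The rule compares post-intervention values. With baselines balanced by randomisation, the expected difference equals the difference in gains.

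**3. Largest observed deficit that still passes.** This is limit − t(0.975; 2n − 2) × SD × √(2/n).
- Fall, SD 2.4: 2.0 − 1.579 = 0.42 at n = 19; 2.0 − 1.365 = 0.63 at n = 25.
- Forward, SD 1.4: 1.9 − 0.921 = 0.98 at n = 19; 1.9 − 0.796 = 1.10 at n = 25. These are 52% and 58% of the whole gain.

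**4. Chance of passing when block PBBT truly keeps half the gain.** Noncentrality = (limit − true deficit) / (SD × √(2/n)), tested at one-sided 0.025 to match the 95% interval.
- Fall, deficit 1.0: 1.0 / (2.4 × √(2/19)) = 1.28, giving 24%; 1.0 / (2.4 × √(2/25)) = 1.47, giving 30%.
- Forward, deficit 0.95: 0.95 / (1.4 × √(2/19)) = 2.09, giving 53%; 0.95 / (1.4 × √(2/25)) = 2.40, giving 65%.
- Backward, deficit 0.95, stated SD 2.0: 30% and 38%.
- All three together, by simulation with SDs 2.4, 1.4 and 2.0: about 4% (correlation 0, n = 19) to 24% (correlation 0.8, n = 25). The between-outcome correlation is an assumption. At correlation 0 and n = 19 the product is 0.239 × 0.530 × 0.296 = 0.037.

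**5. What a half-gain limit would need (fall threshold, limit 1.0, SD 2.4, true difference 0, one-sided 0.025).**
- Unadjusted: power 24% at n = 19 and 30% at n = 25; 80% power needs 92 evaluable per arm.
- Baseline-adjusted at an assumed correlation r between baseline and post values, the SD becomes 2.4 × √(1 − r²). At r = 0.7 this is 2.4 × 0.714 = 1.71, and power is 42–52%. At r = 0.3 to 0.5, power is 26–38%.
- For 80% power, 92 × (1 − 0.49) = 46.9, or about 48 per arm once the covariate's degree of freedom is counted. At r = 0.5, 92 × 0.75 = 69; at r = 0.3, 92 × 0.91 = 84.

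**The case against.** **The rule is stricter than any one outcome suggests.** The plural wording of the decision rule most naturally requires all three outcomes to pass, though it does not say so outright, and both analysis sets are to be used. On the fall threshold at SD 2.4, passing also needs a point estimate that retains about 68–79% of a 2.0 gain (deficit at most 0.63 or 0.42). A reader might infer that a schedule losing most of the benefit would readily be declared non-inferior. The documents do not support that: an arm losing three quarters of the gain passes 9–11% of the time on the fall threshold alone, and about 0.1–6% if all three must pass. This stands and limits the harm. But the protection comes from wide intervals, not from the limit, and on the forward threshold alone a half-gain loss passes more often than not.

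**A smaller SD would look worse.** The post-training SD of 1.3 would raise the half-gain pass rate on the fall threshold to 64–76%. That SD belongs to one arm of 11 patients who all improved; the same section gives 2.0 at baseline and the plan uses 2.40. Applying 1.3 to both arms is unsupported, so it is not used here.

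**The true effect might be smaller than the limit.** A reader might infer this because 4 of 13 comparison patients also improved. A count of improvers gives no mean change. The controlled effect may be below the limit, but it cannot be computed.

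**Assay sensitivity.** One could argue that baseline testing itself trains participants, so that gains in both arms would prove nothing. That is a separate question from the size of the limits, it rests on equating a test with a cited training session, and the protocol relies on the established efficacy of perturbation training.

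**It is a pilot.** The Limitations section says the study has a pilot character. That favours modest wording, but the Statistical Analysis section still fixes a formal non-inferiority rule.

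**Conclusion.** The concern holds. All three limits equal the uncontrolled before-to-after gains of random PBBT in 11 stroke patients, with no other rationale printed. The protocol does not say the limits were derived from those gains; the exact match on three outcomes makes it likely, and the 100% ratio holds either way. Meeting the rule shows only that block PBBT did not lose the whole gain, which falls short of the protocol's own meaning of non-inferiority.

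The size is moderate: a half-gain loss passes 24–30% of the time on the fall threshold, 53–65% on the forward threshold, and about 4–24% if all three must pass. This rests on the planned SDs, 19–25 evaluable per arm, the 95% interval, assumed correlations of 0 to 0.8, and random PBBT gaining as much in relatively fit older adults as it did in stroke patients. It would go too far to say that a passing result carries no information, or that the limits are known to exceed the effect of random PBBT.

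**What to change.** Keep 50 participants. If 2.00, 1.9 and 1.90 are retained, state before the analysis that meeting the rule permits one conclusion: block PBBT did not lose the whole of the gain seen with random PBBT. Report each confidence interval also against a half-gain reference of 1.0 (fall), 0.95 (forward) and 0.95 (backward). The half is illustrative; the documents give no basis for a particular fraction. This suits the pilot character that the protocol claims and costs only wording and one extra line per result, at the price of a weaker headline conclusion.

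If the sponsor prefers tighter limits, it should justify them and restate the power. For a half-gain limit on the fall threshold at SD 2.4, power is 24–30% unadjusted. Reaching 80% needs about 92 evaluable per arm, or about 48 with baseline adjustment at an assumed correlation of 0.7. The Trial Status section puts the end of baseline and post-training data collection at 1 March 2021, days after publication, so this would be a late change and would have to be dated and explained as such.

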**Figure 2 F2:**
[figure not shown]
Details of the intervention training programs.

**Table 2 T2:** Details of the perturbation parameters that were used in the pre-testing and post-testing procedures.

Perturbation size	Displacement (cm)	Velocity (cm/s)	Acceleration (cm/s^2^)
Extra small	3	0.11	0.35
Small	6	0.22	0.7
Medium	9	0.44	1.5
Medium–large	12	0.66	2
Large	15	0.88	2.5
Extra-large	18	1.20	3

*Perturbations during the pre-testing and post-testing procedures will be induced through a mechatronic device that provides controlled and unexpected AP and ML platform translations during standing and walking. Four directional perturbations (right = R/left = L/forward = F/backward = B) in a random order of each of the six magnitudes, for a total of 24 perturbations*.

**Table 3 T3:** Details of the perturbation protocols used in intervention training programs.

Training session	Platform displacement (cm)	Platform peak velocity (cm/s)	Platform peak acceleration (cm/s^2^)	Number of unannounced random* perturbations (per session)	Number of unannounced block* perturbations (per session)
1	1–3 cm	0.11 cm/s	0.35 cm/s^2^	35	35
2	2–4 cm	0.11 cm/s	0.35 cm/s^2^	35	35
3	3–5 cm	0.11 cm/s	0.35 cm/s^2^	35	35
4	4–6 cm	0.22 cm/s	0.7 cm/s^2^	35	35
5	5–7 cm	0.22 cm/s	0.7 cm/s^2^	35	35
6	6–8 cm	0.22 cm/s	0.7 cm/s^2^	35	35
7	7–9 cm	0.44 cm/s	1.5 cm/s^2^	35	35
8	8–10 cm	0.44 cm/s	1.5 cm/s^2^	35	35
9	9–11 cm	0.66 cm/s	2 cm/s^2^	35	35
10	10–12 cm	0.66 cm/s	2 cm/s^2^	35	35
11	11–13 cm	0.66 cm/s	2 cm/s^2^	35	35
12	12–14 cm	0.88 cm/s	2.5 cm/s^2^	35	35
13	13–15 cm	0.88 cm/s	2.5 cm/s^2^	35	35
14	14–16 cm	0.88 cm/s	2.5 cm/s^2^	35	35
15	15–17 cm	1.2 cm/s	3 cm/s^2^	35	35
16	16–18 cm	1.2 cm/s	3 cm/s^2^	35	35

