### Data Collection and Outcome Measures

To assess the feasibility of the study, we will document the number of training sessions attended/missed, reasons for missed sessions, and the rate of missing data for the outcomes described below. In case the participant did not attend more than two consecutive training sessions or four training sessions in total, they will be excluded from the study.

After signing on the consent forms, the participants will complete a questionnaire at baseline that asks about their demographics and medical history and past falls. Participant’s balance reactions will be assessed during standing and walking. Participants will be exposed to right/left/forward/backward unannounced platform translations through a mechatronic device (i.e., BaMPer system; Shapiro and Melzer, 2010) that will be increased systematically and controlled in six perturbation magnitudes in increasing level of difficulty (see Table 2), for a total of 24 perturbation trials in standing: six right, six left, six forward, and six backward. During the walking trials, the participants will be exposed to 12 perturbations, six right and six left, since recovery step initiation in the forward and backward perturbation trials in walking is hard to explore.

During the examination, participants will wear a safety harness that prevents falls but does not otherwise restrict their balance recovery movements. Fall during the assessment session will be defined as load cell sensors detecting 30% or more bodyweight suspended by the safety harness. Participants will wear their own walking shoes and be instructed to react naturally to keep their balance and to prevent themselves from falling in response to perturbations. In case of falling into the harness system, grasping the examiner’s hand, or asking to stop the test by the subject, the examination will be stopped and will not continue to the next level. A seated rest break will be given whenever needed. The data will be analyzed observationally and kinematically for each trial.

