### Step Thresholds in Standing

We will verify single-step threshold, multiple-step threshold, and fall threshold levels, for AP and ML directions, following a loss of balance using the Vicon Motion Analysis Systems (Oxford, UK), allowing image pauses, slow motion, and running of the image back and forth. The single-step threshold level is defined as the minimum perturbation magnitude that consistently elicited a single compensatory step for at least two consecutive perturbation magnitudes. The multiple-step threshold is defined as the minimum perturbation magnitude that consistently elicited a sequence of recovery steps, and the fall threshold is defined as the minimum perturbation magnitude that consistently elicited a fall into the harness system. These step threshold levels were shown previously to be independent predictors of a future fall (Hilliard et al., 2008; Carty et al., 2015).

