### Statistical Analysis

Cohort descriptors and baseline values for primary and secondary outcomes will be compared between groups using Mann–Whitney *U* tests (continuous variables) or Fisher’s exact test (categorical variables). Measures that differ between groups at baseline may be used as covariates in the analysis of primary and secondary outcomes. To test the primary hypothesis, we will calculate the 95% CI for the post-intervention difference between groups (block PBBT minus random PBBT) for the primary outcomes [fall threshold and multiple-step threshold (backward and forward)]. Our hypothesis of non-inferiority will be supported if the lower limits of the 95% CIs are greater than the negative value of the non-inferiority limits (Schumi and Wittes, 2011). We will use both intention-to-treat and per-protocol analyses to test the primary hypothesis, as is recommended (Schumi and Wittes, 2011); per-protocol analysis will include only those participants who completed at least 80% of the training sessions. We will also use paired *t*-tests for each group individually to determine if the groups improve over time in the primary and secondary outcomes. To address the secondary objectives, we use analysis of covariance (ANCOVA) to compare the posttraining voluntary step execution test and postural sway parameters as well as the Berg Balance Score, Late-Life Function and Disability Index, and FES-I scores between groups, with the baseline value for each measure as a covariate. The dependent variable will be rank-transformed prior to conducting the ANCOVA to allow for nonparametric analysis.

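### The fall-threshold limit (2.00) and SD (2.40) come from a study whose post-training mean of 6.5 cannot occur on this trial's six-level test, and any ceiling on that test biases the planned comparison towards non-inferiority

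*Protocol article*

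**What the plan says.** Data Collection and Outcome Measures says the test perturbations are "increased systematically and controlled in six perturbation magnitudes in increasing level of difficulty", and the note to Table 2 gives four directions "in a random order of each of the six magnitudes, for a total of 24 perturbations". Table 2 ends at 18 cm. Under Step Thresholds in Standing, "the fall threshold is defined as the minimum perturbation magnitude that consistently elicited a fall into the harness system". The article gives no value for a participant who passes the top magnitude without falling.

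Power and Sample Size Calculation reports that 11 stroke patients given random PBBT "improved their fall threshold (from 4.5 ± 2.0 to 6.5 ± 1.3"; the number of levels on that study's scale is not stated. The same section plans the trial with a limit of 2.00 and an expected difference of 0.00, assumes that "the common standard deviation for the fall threshold is 2.40", and attributes the SDs to that earlier study.

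Statistical Analysis takes the 95% CI for the post-intervention difference, block minus random, and supports non-inferiority "if the lower limits of the 95% CIs are greater than the negative value of the non-inferiority limits".

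**The concern.** On a six-level test the largest value the definition allows is 6, so a group mean of 6.5 is impossible. The limit and SD therefore rest on a scale, or a scoring rule, that does not match the test as described. If the scale differs, 2.00 levels there is not 2.00 levels here, and the decision rule has no stated basis for this outcome. If the scale is the same and non-fallers were scored above 6, the planning data already show a strong ceiling.

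The second case has a direction. A ceiling compresses the observed difference while the limit stays at 2.00, so the comparison moves towards the hypothesis the trial hopes to support. The participants here are described under Limitations as relatively fit and stroke is an exclusion, so a ceiling is more plausible than in the source study, though the article gives no figure for it.

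**Working it through.** **1. The plan's own sample size.** Inputs from Table 4: one-sided alpha 0.05, power 80%, limit 2.00, SD 2.40, expected difference 0. Normal approximation: n = 2 × (1.645 + 0.842)² × (2.40/2.00)² = 17.8, so 18. The exact noncentral t gives 19 per group (power 80.9%). The stated 19 reproduces. The mean of 6.5 does not enter this formula.

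**2. Where the limit and SD appear to come from.** 6.5 − 4.5 = 2.00, the fall-threshold limit. The multiple-step limits follow the same pattern: 3.8 − 1.9 = 1.90 and 4.5 − 2.6 = 1.90. Also √(2.0² + 1.3²) = 2.39, close to 2.40. The article ties the SDs to the earlier study; that the limits equal its gains is an inference it does not state.

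**3. What 6.5 ± 1.3 implies.** On levels 1–6 it is impossible. If non-fallers were scored 7, the mean is at most 6 plus the share scored 7, so about half or more must be at 7. Listing every set of 11 integers on 1–7 whose mean rounds to 6.5 and SD (divisor n − 1) to 1.3 leaves one set: 3, 5 and nine 7s. Check: (3 + 5 + 63)/11 = 6.45 and √(16.73/10) = 1.29. That is 9 of 11 at the ceiling. On a 1–8 scale, 14 sets fit, with at most 4 of 11 at the top, so a longer scale carries no such implication.

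**4. Effect of a ceiling on the planned rule.** Assumptions: units comparable with the earlier study; normal latent fall level, rounded up to the next test level, floor at 1; SD 1.3, 2.0 or 2.4; 19 or 25 per arm; block truly worse by exactly 2.0; success if the lower 95% limit exceeds −2.00; at least 20,000 simulated trials per setting. Ranges run over SD and arm size. With no ceiling the rule errs in about 2.5% of trials, as it should.

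| Random-arm latent mean | Random arm above level 6 | False non-inferiority, non-fallers scored 7 | Scored 6 |
|---|---|---|---|
| 4.5 | 12–27% | 3–11% | 6–23% |
| 5.5 | 35–42% | 5–15% | 27–40% |
| 6.5 | 58–65% | 25–34% | 62–98% |

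Upper ends move by about a point between runs. At a mean of 6.5 the observed difference shrinks from 2.0 to about 1.3–1.5 (scored 7) or 1.0 (scored 6). At the lower means the floor at level 1 contributes too: without it, the ranges for means 4.5–5.5 are about 3–11% (scored 7) and 5–34% (scored 6).

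**The case against.** Several stronger readings are tempting, and the article does not support them.

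- *The trial was planned on a mean of 6.5, so many participants will never reach a threshold.* The sample size uses only a difference, a limit and an SD. A ceiling share follows only if the earlier study's levels match these six, which is not stated.
- *An SD of 2.40 is impossible at a mean of 4.5.* On 1–6 the bound is √(3.5 × 1.5) = 2.29, but the article pairs 4.5 with SD 2.0, not 2.40. The value 2.40 looks more like the SD of a change, and with divisor n − 1 and 11 patients the bound is 2.29 × √(11/10) = 2.40.
- *Training takes people off the top of the scale.* That assumes a high starting row in Table 3 and a step up every session. Starting in rows 1–3 and moving up each session reaches only rows 8–10 (8–12 cm) by session 8. Training is also during walking, while this threshold is measured in standing.
- *Non-inferiority will be declared falsely.* The simulation covers one of three primary thresholds.

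The simulation itself has limits. The highest figures (scored 6) cannot be combined with an observed 6.5 in the same units, since that scoring cannot produce 6.5. If 6.5 was already a capped mean, the latent mean would be higher than simulated.

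It is also fair that scoring of non-fallers may sit in a fuller document. But the point does not rest on that gap. The mismatch between 6.5 and six levels is on the page, and the printed analysis, an uncensored mean difference against 2.00, errs in the same direction whether non-fallers are scored 6 or 7.

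**Conclusion.** The concern holds in a limited form. Without any assumption, the figures behind the fall-threshold limit and SD come from a study whose post-training mean cannot occur on this test as described, so either the units differ or non-fallers were scored above the top level. With the assumptions in the working, a ceiling raises the chance of wrongly passing this component from 2.5% to about 3–15% (scored 7) or 6–40% (scored 6) for random-arm means of 4.5–5.5, and to about 25–34% or 62–98% at 6.5. The documents do not say where in that range this population lies. The direction does not depend on the case chosen: it favours non-inferiority.

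**What to change.** Before unblinding:

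1. State the scale behind 4.5 and 6.5, including how patients who never fell were scored.
2. Restate the limit, the SD and the resulting power in the six levels of Table 2.
3. Treat participants who complete level 6 without a fall as right-censored, and take the CI from a censored or interval-censored model, alongside the planned mean difference. State how tests that ended early for a reason other than a fall (grasping the examiner's hand, participant request) enter that model.
4. Report the share at the ceiling in each arm. If it is substantial, do not let the fall threshold support non-inferiority on the uncensored mean difference alone.

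This changes wording and analysis and needs no new data. It costs power and adds reliance on a distributional assumption for the censored part. With an interval-censored normal model, no true difference, a latent mean of 6.5 and 25 per arm, power is roughly 95% at SD 1.3, 77% at SD 2.0 and 65% at SD 2.4 (600 simulated trials per setting). False non-inferiority at the limit returns to about 2–3%, but these data were generated from the same normal model, so that figure is a best case.
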